### Concomitant Procedures

Additionally, any non-drug therapies or diagnostic, therapeutic, or surgical procedures performed during the trial will be recorded in the e-CRF, including the date and reason for procedure.

### Special Precautions

Not Applicable

## Medicinal Product Accountability

The Investigator is responsible for ensuring drug accountability, including reconciliation of drugs and maintenance of drug records.

- Upon receipt, the Investigator (or designee) will check for accurate delivery and acknowledge receipt by signing (or initialing) and dating the documentation provided by the Sponsor and returning it to the Sponsor. A copy will be retained for the Investigator File.
- The dispensing of drug will be carefully recorded on appropriate drug accountability forms and an accurate accounting will be available for verification by the Sponsor Monitor at each monitoring visit.
- Drug accountability records will include:
- Confirmation of drug delivery to the trial site.
- The inventory at the site of drug provided by the Sponsor and prepared at the site.
- The use of each dose by each subject.
- The return to the Sponsor or alternative disposition of unused drug.
- Dates, quantities, batch numbers, expiry dates and (for drug prepared at the site) formulation, as well as the subjects’ trial numbers.
- The Investigator should maintain records that adequately document:
- That the subjects were provided the doses specified by the clinical trial protocol/amendment(s), and
- That all drug provided by the Sponsor was fully reconciled.

Unused drug must not be discarded or used for any purpose other than the present trial. Medicinal Product that has been dispensed to a subject must not be re-dispensed to a different subject.

The Sponsor Monitor will periodically collect the drug accountability form and will check all returns (both unused **and** used containers) before arranging for their return to the Sponsor or authorizing their destruction by the trial site.

## Assessment of Medicinal Product Compliance

Subjects should be routinely encouraged by the study personnel to administer all doses of medications over the entire twenty-four weeks of treatment.

Subject compliance will be evaluated by the following:

- Documentation of missed injections in the Study Treatment Administration e-CRF
- Review of diary cards, on which the subjects will enter the dates and times of each of their injections
- Subjects should be instructed to bring with them to each visit both opened and unopened drug packages, in order to allow the assessment of compliance with trial treatment. Drug administration must be recorded in the e-CRF, as applicable.

## Method of Blinding

This trial is open-label. The MRI analysis and immunologic studies will be rater-blinded. Neurologic exams will not be blinded.

## Emergency Unblinding

Not applicable.

## Treatment of Overdose

An overdose is defined as any dose greater than the highest daily dose included in the clinical trial protocol. Any overdose must be recorded in the trial medication section of the e-CRF.

For monitoring purposes, any case of overdose – whether or not associated with an adverse event (serious or non-serious) – must be reported to the Sponsor’s Global Drug Safety department in an expedited manner using the appropriate reporting form [(see Section 7.9.1.11)](#_Procedure_for_Reporting).

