## Summary of Rebif® Clinical Trials

Rebif® has been tested in a series of studies in MS subjects at doses ranging from 22 mcg to 132 mcg weekly, with a dosing frequency ranging qw to tiw. The pivotal trial in RRMS was the 6789 (PRISMS) study (34;35;50;51), a double-blind, placebo controlled randomized trial of 22 mcg tiw or 44 mcg tiw Rebif®. The initial two-year study demonstrated that Rebif® at both doses significantly reduced clinical event rate (32% reduction for 44 mcg tiw relative to placebo, p<0.001), slowed disability progression (Hazard Ratio, [HR]=0.63, p=0.01), and reduced MRI lesion activity (77% reduction T2 active lesions, p<0.0001) and accumulation of new lesion burden (-3.8% compared to +11%, p<0.0001). Rebif® is the only disease modifying agent to have demonstrated efficacy on all four of these measures in RRMS.

A test of the importance of treatment regimen was performed in the 21125 (EVIDENCE) study (52), a direct comparative trial of INF-beta-1a 44 mcg tiw (Rebif®) vs. INF-beta-1a 30 mcg qw (Avonex®) in RRMS. This study demonstrated a 12% absolute difference (75% vs. 63%) in the proportion of subjects remaining clinical event-free over twenty-four weeks (primary outcome), which equates to a 19% relative reduction in the risk of clinical event over one year for Rebif® vs. Avonex® subjects (p<0.001). After forty-eight weeks, there was a 10% absolute difference (62% vs. 52%) in the proportion of subjects remaining clinical event-free, which also equates to a 19% relative reduction in the risk of clinical event over one year for Rebif® vs. Avonex® subjects (p=0.009). The time to first clinical event over forty-eight weeks was also significantly reduced with Rebif® (HR=0.70, p=0.003). The main secondary endpoint was based on serial brain MRI showing a 33% reduction in MRI combined unique active lesions for Rebif® relative to Avonex® (p<0.001) over twenty-four weeks, and 36% relative reduction in T2 lesion activity over forty-eight weeks (p<0.001). This study supports the concept of higher, more frequent IFN-beta dosing being more effective than low dose, low-frequency IFN-beta treatment.

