## Safety Profile of Rebif® based on Clinical Trials

Rebif® has been well tolerated in all clinical pharmacology studies, even at high doses (up to 66 mcg/m2). In later phase clinical trials, Rebif® has been tested across a broad range of doses, for varying duration, and in different stages of MS disease. Dose testing has ranged from 22 mcg to 132 mcg weekly with frequency of administration being daily or thrice weekly. Subject age has ranged from 17 to 68 years.

Additional safety data from clinical trials in all indications studied, post-marketing surveillance and literature reports were compiled in the August 2001 Integrated Summary of Safety that summarized the safety of IFN-beta-1a across several MS and non-MS studies. The majority of exposure is for the specified indication of MS, principally RRMS. The data obtained from this population provide a good understanding of the safety profile of Rebif®.

These data show that, overall, Rebif® is well tolerated at the doses intended for use in the MS population, namely 44 mcg tiw administered by the sc route. The overall mortality rate on treatment is not greater than expected for untreated MS subjects nor is there an excess of serious adverse events on treatment compared to placebo.

The most common adverse events fall into four main categories: injection site reactions (ISRs), flu-like symptoms, hepatic dysfunction and cytopenia. With the exception of ISRs, these events usually occur during the first six months of therapy, are generally mild in severity and usually resolve spontaneously as Rebif® therapy is continued. They rarely require dose reduction or treatment interruption. Other common reactions observed during Rebif® therapy are skin rash, depressive symptoms, and thyroid dysfunction (manifested as hypo- or hyperthyroidism). Details are disclosed in the Rebif®Investigator’s Brochure.

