## Dosage and Administration

**Rebif®**

Rebif® will be supplied in pre-constituted syringes. During the four week titration phase of Rebif®, dosages must be adjusted according to the following dose titration schedule (refer to the locally approved package insert for the administration, storage and handling instructions for Rebif®):

| **Week** | **Recommended Titration** | **Volume** | **IFN-beta-1a dose** |
| --- | --- | --- | --- |
| 1-2 | 20% | 0.1 mL | 8.8 mcg |
| 3-4 | 50% | 0.25 mL | 22 mcg |
| 5 + | 100% | 0.5 mL | 44 mcg |

Source: Rebif® Package Insert: Schedule for Rebif® dose titration.

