# Trial Procedures and Assessments

## Schedule of Assessments

Prior to performing any trial assessments not part of the subject’s routine medical care, the Investigator will ensure that the subject or the subjects legal representative has provided written informed consent according to the procedure described in Section 9.2.

A screening log will be completed for all subjects who sign the Informed Consent Form (ICF) but do not subsequently enter the trial. Subjects will be identified by their initials and dates of birth, and reason(s) for exclusion from the trial will be recorded.

Please refer to [(see Appendix A)](#_Appendix_A_-) for a Schedule of Assessments to be performed during the conduct of this trial, as well as the frequency of testing over twenty-four weeks of treatment and the four-week, post-treatment telephone call.

In summary, subjects who sign an institutional review board approved ICF and who satisfy the eligibility criteria at Screening should then return to the clinic on Study Day 1, Week 12 and Week 24/Exit. The subjects will also receive a telephone call four weeks post-treatment to monitor their status and well-being.

Due to the workload of the clinic, as well as subjects’ own personal schedules, it is understood that there may be conflicts in subjects returning to the clinic on the exact day of their specified contacts. As such, a “window” of  seven days is permitted for subjects to be evaluated at each scheduled contact (Study Day 1, Week 12, Week 24 and Week 28 (telephone call).

Subjects will be asked to keep diary cards to collect information regarding treatment administration, concomitant medications, concomitant procedures and any adverse event(s) they experienced. This information will be discussed with each subject, and once confirmed by the Investigator or study personnel, it will be recorded in the appropriate e-CRF.

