**RRMS Subjects**

The following assessments must be performed:

- Re-confirmation that eligibility criteria are satisfied
- For female subjects of childbearing potential, a urine pregnancy test, to be performed locally at the study site
- Blood collection for Immunological Samples
- MRI
- Injection Training/Dispensing of Rebif®
- Provide each subject with a diary card and train on proper completion to record injection dates/times, concomitant medications/procedures and adverse events

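### The overdose definition in Section 6.9 uses one daily ceiling of 44 mcg, so a full syringe during titration, or injections more often than three times a week, triggers no overdose record or expedited report

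*Protocol*

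**What the plan says.** Section 6.9 of the protocol gives the only definition of overdose: "An overdose is defined as any dose greater than the highest daily dose included in the clinical trial protocol". Two duties depend on it. An overdose has to be entered in the trial medication part of the e-CRF, and it has to go to the sponsor's drug safety department by the expedited route, with or without an adverse event.

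Section 6.1 sets the doses: "During the four week titration phase of Rebif®, dosages must be adjusted according to the following dose titration schedule". The table gives 8.8 mcg (0.1 mL) in Weeks 1-2, 22 mcg (0.25 mL) in Weeks 3-4 and 44 mcg (0.5 mL) from Week 5. Section 3.2 describes the product as a 0.5 mL pre-filled syringe holding 44 mcg. The Synopsis sets three injections a week for 24 weeks.

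Other sections record how the drug is used:
- Section 6.5 lists among the accountability records "The use of each dose by each subject", and used containers are returned.
- Section 6.6 provides for "Review of diary cards, on which the subjects will enter the dates and times of each of their injections".
- On Study Day 1 (Section 7.2.2.1) the list includes "Injection Training/Dispensing of Rebif".
- Section 7.1 says that subjects "should then return to the clinic on Study Day 1, Week 12 and Week 24/Exit".
- Section 5.4.5 makes withdrawal from study treatment mandatory for protocol violations, and it counts non-compliance among them.

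**The concern.** A single ceiling set at the full maintenance dose does not fit a schedule that starts at one fifth of that dose and is given on three days a week. Each syringe described holds 0.5 mL, while Weeks 1-4 call for 0.1 or 0.25 mL, so injecting the whole syringe is a foreseeable mistake. It is also one that a threshold of more than 44 mcg can never catch. The same holds for injecting too often, as long as no day exceeds 44 mcg.

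Section 6.9 evidently wants the drug safety department to hear quickly of excess dosing even when nothing has gone wrong clinically. Section 2 explains that there is no data monitoring committee and gives that department the oversight of safety. Under the present wording, these errors would reach it only through routine data review.

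**Working it through.** **Inputs.** Full dose 44 mcg in 0.5 mL (Section 3.2); titration steps of 20%, 50% and 100% (Section 6.1); three injections a week for 24 weeks (Synopsis); overdose means more than the highest daily dose (Section 6.9). I read that highest daily dose as 44 mcg, the largest dose this trial schedules, and I read a dose as the total for one day.

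**The plan's own doses.** The concentration is 44/0.5 = 88 mcg/mL.
- Weeks 1-2: 0.20 × 44 = 8.8 and 0.1 × 88 = 8.8 mcg.
- Weeks 3-4: 0.50 × 44 = 22 and 0.25 × 88 = 22 mcg.
- Week 5 on: 1.00 × 44 = 44 and 0.5 × 88 = 44 mcg.

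The table in Section 6.1 is reproduced.

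**The present rule applied to four cases.**

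| Case | Given | Scheduled | Ratio | Most in one day | Above 44 mcg? |
|---|---|---|---|---|---|
| One full syringe, Weeks 1-2 | 44 mcg | 8.8 mcg | 44/8.8 = 5 | 44 mcg | No |
| One full syringe, Weeks 3-4 | 44 mcg | 22 mcg | 44/22 = 2 | 44 mcg | No |
| Fourth injection in a week, from Week 5 | 4 × 44 = 176 mcg/week | 3 × 44 = 132 mcg/week | 1.33 | 44 mcg | No |
| Daily injection, from Week 5 | 7 × 44 = 308 mcg/week | 132 mcg/week | 2.33 | 44 mcg | No |

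On weekly totals, one full syringe in Weeks 1-2 gives 44 + 2 × 8.8 = 61.6 against 3 × 8.8 = 26.4 mcg (2.33 times). In Weeks 3-4 it gives 44 + 2 × 22 = 88 against 3 × 22 = 66 mcg (1.33 times).

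**Would another rule produce the report?**
- Section 6.6 specifies injection dates and times in the diary but not volume. Excess frequency would show there; a full syringe in Weeks 1-4 need not.
- Sections 6.5 and 6.6 attach no expedited report to what they find.
- Section 5.4.5 leads to withdrawal, not to an expedited report.
- Section 7.9.1.11 starts its 24-hour clock from a serious adverse event.

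**How many injections are in the titration phase.** 4 weeks × 3 = 12 of 24 × 3 = 72 per subject (16.7%); for 25 subjects, 300 of 1,800. These are scheduled injections, not errors.

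**The proposed rule applied to the same cases.** 44 ≥ 22 in Weeks 1-2: reported. 44 ≥ 44 in Weeks 3-4: reported. Four or seven injections in a week exceed three: reported. Two full syringes on one day, 88 > 44: still reported, because the daily ceiling stays. A slip of 0.15 mL instead of 0.1 mL, 0.15 × 88 = 13.2 < 22 mcg: not reported.

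**The case against.** The strongest reply is that nothing here contradicts anything else. Section 6.9 sets a ceiling, Section 6.1 sets a schedule, and a dose off schedule but no higher than the trial's full dose can fairly be called a dosing deviation. The titration column is headed as a recommendation, the product is marketed with a known safety profile, and this is a pilot in 25 patients. All of that stands as an argument for low severity. It does not remove the mismatch: the governing sentence in Section 6.1 says that doses must be adjusted, and Section 6.9 wants reports even without an adverse event.

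Three stronger readings are tempting, and the documents support none of them.

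- *These errors would go undetected.* Diaries, returned containers, accountability records and the withdrawal rule could all reveal them. What is missing is the expedited report. Nor is late discovery a fault of Section 6.9. No visit is scheduled between Study Day 1 and Week 12, about 8 weeks after titration ends, and rewording the definition adds no earlier contact.
- *Daily 44 mcg is an untested and harmful exposure because 308 exceeds 132 mcg a week.* Section 3.9 gives "doses ranging from 22 mcg to 132 mcg weekly, with a dosing frequency ranging qw to tiw". Section 3.10 says "Dose testing has ranged from 22 mcg to 132 mcg weekly with frequency of administration being daily or thrice weekly" of later-phase trials. The same section also reports good tolerability in clinical pharmacology studies up to 66 mcg/m². If body surface is assumed to be 1.5 to 2.0 m² (not in the protocol), that is 66 × 1.5 = 99 to 66 × 2.0 = 132 mcg, or 2.25 to 3 times 44 mcg. The 132 mcg figure therefore does not bound all earlier exposure, and expected harm from the errors at issue is low.
- *Some 300 of 1,800 injections would be misreported.* That is the number of titration injections. The protocol gives no error rate.

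**Conclusion.** The point holds, as a minor one. As worded, Section 6.9 cannot classify as overdose a full syringe in Weeks 1-2 (5 times the scheduled dose) or in Weeks 3-4 (2 times), nor injections more often than three times a week at up to 44 mcg a day (up to 308 against 132 mcg a week). Without a serious adverse event, no other section leads to an expedited report of these errors.

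The conclusion rests on reading the highest daily dose as 44 mcg and a dose as a daily total. If a dose meant a single injection, two full syringes on one day would escape as well, so the gap would be wider. The consequence is confined to safety reporting. How often such errors would occur is unknown, and the primary analysis is unaffected.

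**What to change.** In Section 6.9, keep the present threshold and state it as a daily total: more than 44 mcg in one day. Then add three further triggers: in Weeks 1-2, a daily dose of 22 mcg or more; in Weeks 3-4, a daily dose of 44 mcg or more; and more than three injections in a study week, except where a shift of injection day is documented. The daily ceiling must stay. A rule based only on single injections and a weekly count would miss two full syringes on one day followed by one later that week.

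In Section 6.6, have the injected volume for Weeks 1-4 entered in the diary and in the Study Treatment Administration e-CRF.

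The cost is a short addition to Section 6.9, one extra field for 12 injections per subject (12 × 25 = 300 entries), and possibly a few more expedited reports. The thresholds sit at the next titration step, 22/8.8 = 2.5 times the scheduled dose in Weeks 1-2 and 44/22 = 2 times in Weeks 3-4, so small volume errors stay out. The two multiples differ slightly, which is a fair price for thresholds that staff can read directly from the dosing table.

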## Medical Care of Subjects after End of Trial

After a subject has completed the trial or has withdrawn early, usual treatment will be administered, if required, in accordance with the trial site’s standard of care and generally accepted medical practice and depending on the subject’s individual medical needs.

# Trial Procedures and Assessments

## Schedule of Assessments

Prior to performing any trial assessments not part of the subject’s routine medical care, the Investigator will ensure that the subject or the subjects legal representative has provided written informed consent according to the procedure described in Section 9.2.

A screening log will be completed for all subjects who sign the Informed Consent Form (ICF) but do not subsequently enter the trial. Subjects will be identified by their initials and dates of birth, and reason(s) for exclusion from the trial will be recorded.

Please refer to [(see Appendix A)](#_Appendix_A_-) for a Schedule of Assessments to be performed during the conduct of this trial, as well as the frequency of testing over twenty-four weeks of treatment and the four-week, post-treatment telephone call.

In summary, subjects who sign an institutional review board approved ICF and who satisfy the eligibility criteria at Screening should then return to the clinic on Study Day 1, Week 12 and Week 24/Exit. The subjects will also receive a telephone call four weeks post-treatment to monitor their status and well-being.

Due to the workload of the clinic, as well as subjects’ own personal schedules, it is understood that there may be conflicts in subjects returning to the clinic on the exact day of their specified contacts. As such, a “window” of  seven days is permitted for subjects to be evaluated at each scheduled contact (Study Day 1, Week 12, Week 24 and Week 28 (telephone call).

Subjects will be asked to keep diary cards to collect information regarding treatment administration, concomitant medications, concomitant procedures and any adverse event(s) they experienced. This information will be discussed with each subject, and once confirmed by the Investigator or study personnel, it will be recorded in the appropriate e-CRF.

## Assessments to be performed at each scheduled visit

The assessments to be performed and/or information to be obtained at each respective clinic visit or telephone contact are as follows:

### Screening Period

**RRMS Subjects**

The following information should be obtained at Screening (within 14 days prior to Study Day 1):

- A signed institutional review board (IRB) approved ICF and HIPAA Authorization (provide a copy to the subject, as well as retain a copy for the Investigator File).
- Medical History, including:
- Demographic data, including date of birth, gender and race
- Review of eligibility criteria
- Relevant medical history, including past and ongoing medical conditions related to MS
- For female subjects, birth control methods will be discussed and recorded
- Recording of adverse events and concomitant medications/procedures
- Physical examination unrelated to MS, including height, weight and vital signs [(see Section 7.2.6.1)](#_Physical_Examinations)
- Neurological assessment (full exam including EDSS) [(see Section 7.2.6.2)](#_Neurological_Assessments)
- Laboratory Assessments (Chemistry, Hematology, ferritin, transferrin, uric acid)
- A blood sample will be collected for analysis of thyroid function tests.
- Serum pregnancy test for female subjects of childbearing potential

**NOTE: Confirmation that a subject is not pregnant must be confirmed by a negative serum beta human chorionic gonadotropin (hCG) test within 14 days prior to Study Day 1 (the first day of dosing) and by a negative urine pregnancy test on Study Day 1.**

**Healthy Control Subjects**

The following information should be obtained at Screening (within 14 days prior to Study Day 1):

- A signed institutional review board (IRB) approved ICF and HIPAA Authorization (provide a copy to the subject, as well as retain a copy for the Investigator File).
- Medical History, including:
- Demographic data, including date of birth, gender and race
- Review of eligibility criteria
- Relevant medical history, including past and ongoing medical conditions
- Recording of adverse events and concomitant medications/procedures
- Physical examination unrelated to MS, including height, weight and vital signs [(see Section 7.2.6.1)](#_Physical_Examinations)
- Neurological assessment (full exam, not including EDSS) [(see Section 7.2.6.2)](#_Neurological_Assessments)

### Treatment Period

The treatment period begins with the completion of all baseline evaluations and the initiation of study treatment on Study Day 1 and continues through to the completion of the treatment period at the Week 24/Exit visit.

#### Study Day 1

